## Abstract

**Background:**

Tobacco smoking is still a worldwide health risk. Current pharmacotherapies have at best, a success rate of no more than 50%. Auricular (ear) acupressure has been purported to be beneficial in achieving smoking cessation in some studies, while in others has been deemed insignificant. We hereby describe the protocol for a three-arm randomised controlled trial to examine the possible benefits of self-administered acupressure for smoking cessation.

**Methods:**

Sixty consenting participants with confirmed habit of tobacco smoking will be recruited and randomized into three arms to receive either auricular acupressure at five true acupoints (NADA protocol), auricular acupressure at five sham points, or no auricular acupressure at all. Participants having auricular acupressure will exert firm pressure to each acupoint bilaterally via the bead in the attached plasters whenever they feel the urge to smoke. The treatment phase will last for six weeks during which all participants will be assessed weekly to review their smoking log, state of abstinence, end-exhalation carbon monoxide levels and possible adverse effects including withdrawal reactions and stress levels. At any time, a successful quit date will be defined with continuous abstinence for the following consecutive 7 days. From then on, participants will be evaluated individually for continuous abstinence rate (CAR), end-exhalation carbon monoxide levels and adverse effects of stress and withdrawal at specified intervals up to 26 weeks. Expectancy of treatment will be assessed with a four-item Borkovec and Nau self-assessment credibility scale during and after intervention.

**Discussion:**

We incorporate validated outcome measures of smoking cessation into our randomised controlled trial design with the objectives to evaluate the feasibility and possible benefits of self-administered auricular acupressure as a non-invasive alternative to pharmacotherapy for smoking cessation.

**Trial Registration:**

ClinicalTrials.gov: NCT01389622 (registered Jul 7 2011)

## Background

### Problem of tobacco smoking

Despite a decreasing trend in some countries, tobacco smoking is still prevalent in about one third of our world's population [1] and it remains a major modifiable health hazard with causative links to increased cardiovascular and pulmonary morbidity. It is also associated with lung cancer, oral cancer, laryngeal carcinoma, esophageal carcinoma, hepatocellular carcinoma, pancreatic carcinoma, bladder cancer and cervical carcinoma[2,3]. In Southeast Asia region, there has been a disturbing increase in adolescent smoking[4]. In 2006, it has been estimated that the annual death toll due to tobacco smoking approached 5 million, and is expected to be doubled by 2030[5]. Unfortunately, success of tobacco control is very much predicated by political constraints and the varying efficacies of smoking cessation strategies in any given locality.

### Methods of smoking cessation

Various methods of smoking cessation are available and can be broadly divided into pharmacological and non-pharmacological methods, which often work better in combination[6]. Nicotine replacement therapy is one of the commonest prescribed treatments which enhances the overall rate of quitting by 50-70%[7] with a stand-alone success rate of 6-20%[8-10]. Newer oral medications include sustained-release bupropion[11] and varenicline[12], which significantly improve smoking abstinence with a higher success rate of 30-50%[11-14]. Thus said, the quote success rates may vary according to the length of continuous abstinence which can range from 3 months to 2 years.

### Auricular acupuncture and smoking cessation

Use of acupuncture for smoking cessation has been practised during the last five decades and its efficacy has been quoted as approaching 45%, which is on par with other pharmacological methods[15]. Auricular (ear) acupuncture is a popular variant with varying degrees of reported efficacy. The practice of auricular acupuncture is based on the theory that there are specific points on the auricle which correspond to major organs or systems of the human body; and they can be manipulated by acupuncture or acupressure to exert a therapeutic effect upon the corresponding target organ or system. An excellent review has been published by Chen in 1993[16]. A recent study shows that electro-stimulation of certain auricular points can modulate vagal activity[17]. A map of commonly used auricular points is included in Figure 1. For smoking cessation, there are various suggested protocols and the 5-points National Acupuncture Detoxification Association (NADA) protocol is the most widely adopted one (5 annotated arrows in Figure 1).

**Figure 1 F1:**
[figure not shown]
**Auricular points as they are used in acupuncture**. The five auricular points chosen according to the National Acupuncture Detoxification Association (NADA) protocol: Autonomic Point (1); Shen Men (2); C. Kidney (3); Liver (4); Lung 2 (5).

A literature search from all available PubMed listings using the following keywords "Auricular acupuncture" and "smoking" only returns 35 entries with the earliest report of a letter in French in 1975[18]. Since then studies have shown[19-23] conflicting results ranging from statistically significant advantage[23] to not effective as compared to placebo[19,21]. Earlier Cochrane reviews in 2000[24] and 2002[25] both asserted that there was no clear evidence for acupuncture in auricular or non-auricular form for smoking cessation. However, since then clinical data [26-29] has continued to report significant benefits of auricular acupuncture and this led Cochrane Review to amend its position in a meta-analysis conducted in 2006, which concluded that "auricular acupuncture appears to be effective for smoking cessation, but the effect may not depend on point location"[30].

### Auricular acupressure versus needle auricular acupuncture

In the literature, there are two types of auricular acupuncture: with needle inserted into the acupoints or with pressure exerted at the acupoints via plastered beads. Needle auricular acupuncture involves skin penetration and carries the usual risks for acupuncture, i.e., hematoma and infection which may lead to otitis externa[31], auricular chondritis and ear deformity[32] or even subacute bacterial endocarditis[33]. Auricular acupressure via plastered beads is relatively non-invasive and can be self-administered by the recipient at times required. According to the published literature, auricular acupressure has comparable efficacy versus needle auricular acupuncture[30].

To date smoking cessation studies using auricular pressure have been sparse with conflicting results, from no better than sham[34,35] to clinically significant [26,36]. However in those studies, the number and choice of auricular points were not standardised and different types of sham treatments were used. Moreover, the outcome measures (i.e., definition of successful abstinence) were not uniform. In view of this, we design our randomised controlled pilot study to test the hypothesis that self-administered auricular acupressure is a safe and feasible method for smoking cessation, with the aim to calculate the sample and effect size for future randomised double-blind placebo controlled trials.

## Methods/design

### Study aim

To demonstrate that self-administered acupressure at verum auricular acupoints is a safe and feasible option for smoking cessation, and when administered at verum acupoints whether it has benefits as compared to acupressure on non-acupoints and that without acupressure.

### Study design

This is a pilot study designed as a 3-arm randomised controlled trial. Eligible participants will be recruited from Queen's University Family Health Team (QUFHT) out-patient clinics as per inclusion and exclusion criteria. They will be randomly allocated to self-administered auricular acupressure at true points, self-administered auricular acupressure at sham points, or no auricular acupressure at all. Figure 2 provides an outline of the study.

**Figure 2 F2:**
[figure not shown]
**Flow chart of proposed pilot study**.

### Recruitment

Recruitment of participants will be based at the out-patient clinics of the Queen's University Family Health Team (QUFHT) in Kingston, Ontario, Canada. Information pamphlet will be placed in the clinics' waiting areas, supplemented by posters and appropriate referral from physicians in the QUFHT. Respondents will be contacted by research assistants from the Centre of Studies in Primary Care (CSPC) and then invited to an initial screening visit for eligibility.

### Inclusion criteria

Participants are considered eligible if they satisfy the following criteria:

• Male or female, between 18 and 75 years of age inclusive, and able to provide informed consent

• History of tobacco cigarette smoking for at least 6 months.

• Confirmed intention of smoking cessation with no more than 2 previous failed attempts in the last 3 years

### Exclusion criteria

Participants will be excluded if they have:

• Doubts about smoking cessation

• Existing pharmacotherapy for smoking cessation

• History of major psychiatric disorder or chronic pain syndromes

• More than 2 failed attempts of smoking cessation in the previous 3 years, either with pharmacological methods or any forms of acupuncture/acupressure.

• History of substance abuse

• History of atopy, or suspected/known allergy to plaster

### Sample size calculation and randomisation

A convenience sample size of a total of 60 participants will be recruited, with 20 participants per arm after randomisation. Compared to other pilot studies, this sample size is deemed sufficient and appropriate statistical methods will be adopted to accommodate for foreseeable limitations during final analysis (see section on statistical analysis). Randomisation and allocation of subjects will be performed according to the CONSORT standards in terms of randomisation type[37], randomisation generation[38], allocation concealment[39]. All participants will be informed that they will be randomly allocated to one of the three study arms using a computer generated sequence created by the SPSS 11.0 (IBM^© ^SPSS^© ^Statistics, NY, USA). The random allocation will only be disclosed on the date of treatment commencement. Apart from Arm 3 (passive controls with no acupressure), blinding will be ensured in participants of Arm 1 (true acupuncture points) and Arm 2 (sham points). In particular, participants receiving acupressure will be told that the actual points chosen may vary over time to eliminate guessing amongst them during the study. Efforts will also be made to avoid contacts between all participants.

### Auricular acupressure

Auricular acupressure will be administered by research assistants and staff nurses who will attend a one-day training course. They will be naïve to the differences between the true and sham acupressure points, and will be advised not to discuss anything with the participants. Their competence and point accuracy will be assessed before the start of the study and periodically thereafter by the research team and two licenced practitioners in acupuncture.

### Verum acupressure (arm 1)

Participants in Arm 1 will receive a 2 mm × 2 mm acupressure plaster (each with a single *Melastoma candidum *seed, see Figure 3a and 3b) at each of the 5 auricular acupoints bilaterally (Lung 2, Shen Men, Autonomic Point, Liver and C. Kidney) according to the NADA protocol (Figure 1). Participants will be instructed to exert firm digital pressure to each acupoint for five seconds via the central plastered seeds whenever they feel the urge to smoke. The seeded plasters are water resistant and should remain in position until the next weekly scheduled review, when they will be replaced with new ones. If the plasters detach, the participants will return to the research center for replacement without delay. Period of intervention will be six weeks (week 2 to week 7).

**Figure 3 F3:**
[figure not shown]
**Figure 3a, b**. Auricular acupressure plasters using *Melastoma candidum *seeds as beads attached under plasters which are individually packaged.

### Sham acupressure (Arm2)

As active controls, participants in Arm 2 will receive identical acupressure plasters bilaterally as in Arm 1 except that the 5 auricular points are randomly chosen with none belonging to the NADA points, or any other true acupressure points that have been described. If in doubt, the principal investigators will be consulted. As in Arm 1, participants in Arm 2 will also be instructed to exert firm digital pressure to every acupoint via the plastered seeds for five seconds whenever they feel the urge to smoke. Similarly, if the plasters detach at any time of the study, they need to be replaced without delay. Period of treatment will be six weeks (week 2 to week 7).

### Control arm (Arm3)

Participants in Arm 3 will serve as passive controls and no acupressure plasters will be administered. For six weeks (week 2 to week 7) they will be given advice and counselling support for smoking cessation during the weekly review, and will be assessed for outcome measures as with the participants in the other two study arms.

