### Co-existent treatment

A record of co-existent treatments, both pharmacological and non-pharmacological, will be recorded for every participant. Any treatment pertaining to smoking cessation should be discontinued at the start of the run-in week and will not be resumed until the participant completed the study or is withdrawn from the study due to treatment failure or adverse events. Equally, all participants will be advised not to attempt any smoking cessation 2 weeks before the run-in period.

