### Statistical analysis

Baseline characteristics of participants (age, number of cigarettes smoked per day, history of packed-years and number of previous cessation attempts) in all the three arms will be expressed as mean values ± standard deviation (SD). The null hypothesis will be adopted in comparing the outcomes (PAR, CAR, CO levels, MNWS score and SCL scores) between Arm 1 and Arm 3, Arm 2 and Arm 3, and finally between Arm 1 and Arm 2. In view of the small sample size for each arm, the Mann-Whitney-Wilcoxon two-sample rank sum test will be used for each Arm pair. Medians will be calculated with the quartiles and the Mann-Whitney *U*. Where possible, treatment effect for each Arm pair comparison will be expressed using the Hodges-Lehmann estimator with the 95% confidence intervals and significance levels.

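### As written, only Arm 3 receives weekly cessation counselling, so both comparisons with Arm 3 mix the absence of acupressure with the presence of counselling

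*Protocol article*

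**What the plan says.** The Control arm (Arm3) section describes Arm 3 as a passive control without plasters and then adds: "For six weeks (week 2 to week 7) they will be given advice and counselling support for smoking cessation during the weekly review". The sentence ends by saying that these participants are assessed for outcomes like those in the other two arms.

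The Verum acupressure (arm 1) section lists plasters at five points on each ear, an instruction to press them when the urge to smoke comes, and weekly replacement. The Sham acupressure (Arm2) section repeats these elements by cross-reference, for example "As in Arm 1, participants in Arm 2 will also be instructed to exert firm digital pressure to every acupoint". Neither section mentions advice or counselling.

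Under Co-existent treatment, "A record of co-existent treatments, both pharmacological and non-pharmacological, will be recorded for every participant", and "Any treatment pertaining to smoking cessation should be discontinued at the start of the run-in week and will not be resumed" until the participant completes or leaves the study.

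The Study aim asks whether true-point acupressure has "benefits as compared to acupressure on non-acupoints and that without acupressure". The Statistical analysis section plans outcome comparisons "between Arm 1 and Arm 3, Arm 2 and Arm 3, and finally between Arm 1 and Arm 2". The trial has 60 participants, "with 20 participants per arm after randomisation".

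**The concern.** Smoking-cessation counselling is itself an intervention aimed at the trial's outcomes. If it goes only to the arm without acupressure, a comparison of Arm 1 or Arm 2 with Arm 3 no longer estimates the effect of acupressure against nothing. It estimates acupressure without counselling against counselling without acupressure. If counselling helps people quit, that component makes acupressure look less beneficial than it is.

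The problem cannot be repaired at analysis. No participant receives both components and none receives neither, so the data carry no information that would separate the two. The article would also be calling an arm passive when it receives a cessation intervention, and readers would take the Arm 3 result as an estimate against no treatment.

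**Working it through.** **Step 1. Compare what each arm is stated to receive in weeks 2 to 7.**

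| | Arm 1 | Arm 2 | Arm 3 |
|---|---|---|---|
| Plasters and pressing instruction | yes, true points | yes, sham points | no |
| Weekly review with assessments | yes | yes | yes |
| Cessation advice and counselling | not stated | not stated | yes |

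The assessments common to all arms are listed in the Abstract (Methods) and under Outcome measures: smoking log or cigarette count, abstinence, carbon monoxide, withdrawal, stress and adverse effects. Neither place includes counselling. The Control arm sentence does refer to the other two arms, but its comparison follows the clause on outcome assessment, and that is its nearest reading. The rule on co-existent treatment covers non-pharmacological care and stops outside cessation treatment, so support from elsewhere should not be expected to even out the arms.

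**Step 2. Count participants by combination.** The stated total reproduces: 3 × 20 = 60. Then:

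- acupressure, no stated counselling: 20 + 20 = 40
- counselling, no acupressure: 20
- both: 0
- neither: 0

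The two factors are fully aliased in Arm 1 v Arm 3 and in Arm 2 v Arm 3, which is 2 of the 3 planned contrasts. Arm 1 v Arm 2 is not affected.

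**Step 3. Size of the shift.** One participant in an arm of 20 is 1/20 = 5 percentage points. Each Arm 3 participant who quits because of counselling therefore lowers the observed difference by 5 points.

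**Step 4. Illustration.** The protocol gives no expected quit rates by arm, so these are assumptions: Arm 1 at 30%, no treatment at 10%, and counselling adding *c* to Arm 3. The difference is 0.30 − (0.10 + *c*), and the 95% half-width is 1.96 × √(p₁(1 − p₁)/20 + p₃(1 − p₃)/20).

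| *c* | Arm 3 rate | Difference | Half-width |
|---|---|---|---|
| 0 | 10% | 20 points | 1.96 × √(0.30×0.70/20 + 0.10×0.90/20) = 24.0 points |
| 5 points | 15% | 15 points | 1.96 × √(0.30×0.70/20 + 0.15×0.85/20) = 25.5 points |
| 10 points | 20% | 10 points | 1.96 × √(0.30×0.70/20 + 0.20×0.80/20) = 26.7 points |

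As a share of the assumed 20-point effect, the shift is 5/20 = 25% to 10/20 = 50%. Over a wider assumed range (acupressure 20 to 40%, no treatment 5 to 10%) the difference always falls by the full counselling gain. At 20% against 10%, a 10-point gain brings it to zero. In the tabulated cases the half-width is at least 24 points, so a shift of 5 or 10 points would not be noticeable in the pilot data.

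**The case against.** The strongest reply is that the concern reads silence as exclusion. No sentence says that Arms 1 and 2 go without counselling, and a journal article may leave background support to the full protocol. The arm descriptions are not exhaustive: the sham section also omits the weekly review and outcome assessment, yet nobody would conclude that Arm 2 lacks them. Counselling is placed at a visit that everyone attends, and the closing phrase of the Control arm sentence can be read as covering counselling as well as assessment. Elsewhere Arm 3 is defined only by what it lacks, as in "Apart from Arm 3 (passive controls with no acupressure), blinding will be ensured in participants of Arm 1", which fits common counselling better than an extra treatment for controls. The flow chart (Figure 2), which is not shown, might settle it. A counselling comparator would also be a legitimate choice for people who want to quit.

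Much of this stands as a limit on confidence. Common support may well have been intended, and the rates in the illustration are assumed. The net bias cannot be derived either, because participants in Arm 3 know that they have no acupressure, and expectancy could push the difference the other way. The instruction that plaster staff should not discuss anything with participants is not evidence here, since it probably serves blinding.

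It does not remove the point. The review visits and assessments omitted from the sham section are assigned to all participants elsewhere; counselling is assigned to one arm and nowhere to the others. The article states a co-intervention and places it in a single arm, which is different from leaving detail out. If a counselling comparator was meant, the passive label and the wording of the aim are wrong.

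**Conclusion.** The concern holds for the text as written, with moderate confidence. Two of three planned contrasts, and one of the two comparisons in the aim, do not isolate acupressure. The counselling component, if effective, works against acupressure in both. The loss is 5 points of abstinence difference per Arm 3 participant who quits because of counselling; on the assumed 30% and 10% rates, a gain of 5 to 10 points is 25 to 50% of the effect. The actual counselling effect and the net direction of bias cannot be obtained from the document.

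True versus sham is unaffected, and so is the effect size it would supply for the later placebo-controlled trial named in the Background. The conclusion depends on Arms 1 and 2 receiving no counselling. If they do receive it, the fault is in the wording only. It should be corrected in either case, because staff following the current text would deliver support unequally and the data could not show it afterwards.

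**What to change.** State in the Verum, Sham and Control arm sections that the same advice and counselling, in content and length, is given at the existing weekly review in all three arms. In the Auricular acupressure section, limit the instruction to plaster staff to not discussing point identity or allocation, so that they can deliver this support.

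If counselling is meant for Arm 3 only, drop the passive-control label and describe the Arm 3 comparisons in Study aim, Study design and Statistical analysis as acupressure versus counselling.

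The cost is one sentence per arm description. If counselling is not already common, it adds up to 40 × 6 = 240 short contacts at visits already scheduled. At an assumed 5 to 10 minutes each, that is 240 × 5/60 = 20 to 240 × 10/60 = 40 staff hours. Sample size, visit schedule and tests do not change.

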### Co-existent treatment

A record of co-existent treatments, both pharmacological and non-pharmacological, will be recorded for every participant. Any treatment pertaining to smoking cessation should be discontinued at the start of the run-in week and will not be resumed until the participant completed the study or is withdrawn from the study due to treatment failure or adverse events. Equally, all participants will be advised not to attempt any smoking cessation 2 weeks before the run-in period.

### Baseline evaluation

Once eligibility is confirmed, all participants will undergo a pre-treatment baseline evaluation during week 1 (run-in period). All subjects will be subjected to a brief physical examination recording the weight, height, body-mass-index (BMI), waist circumference, resting blood pressure, resting heart rate and end-expiratory carbon monoxide level (CO) through the use of a hand-held Smoklyzer^©^. In addition, a brief history will be taken regarding their past and present health. Their smoking profile will also be assessed in terms of number of cigarettes smoked per day, smoking history in terms of pack-years, number of previous attempts of smoking cessation and methods used, and finally, their level of motivation to quit on Likert scale of 0-7.

